### Interventions and assessment procedures

If a recruited participant fulfils the eligibility criteria, the inclusion procedure begins with a screening visit. During the screening visit, the PI or a delegated clinician verifies the eligibility criteria and evaluates the competency of the patient, willingness and ability to comply with the protocol. If the participant and informal caregiver give written consent, the patient is formally included in further assessment.

The screening visit includes medical history, standard physical examination (vital signs, weight, height, orthostatic blood pressure and optionally smell test), neurological examination with focus on extrapyramidal symptoms (UPDRS-III), and ECG. During the visit, we also perform also extended cognitive examination (including MMSE 3rd Norwegian revised Edition) (MMSE-NR3, five different sub-versions to minimize the training effect) (Folstein et al., 1975), the clock test (CT), the Consortium to Establish a Registry for Alzheimer’s Disease (CERAD) word list test (Fillenbaum et al., 2008), the Visual Object and Space Perception (VOSP) battery subtest silhouettes (Warrington and James, 1991), Trail Making Test A and B (TMT A and B) (Reitan and Wolfson, 1985) and the Controlled Oral Word Association Test (COWAT) phonemic fluency FAS test (COWAT-FAS) (City, 1986). We also screen psychiatric and dementia symptoms using standardised tools, such as the Geriatric Depression Scale (GDS) for depression and the Clinical Dementia Rating-Sum of Boxes (CDR-SB) for staging of dementia. Caregiver interviews includes the Mayo Sleep Questionnaire (MSQ) to assess sleep disturbances, the Mayo Fluctuations Scale (MFS) to assess fluctuations, the Neuropsychiatric Inventory (NPI) for neuropsychiatric symptoms, the Relative Stress Scale (RSS) and the Informant Questionnaire on Cognitive Decline in the Elderly.

The next steps are to perform obligatory examinations (MRI cerebrum, DaTSCAN/CIT-SPECT, lumbar puncture, rsEEG and blood taking) within a maximum of 90-day period from the screening day. After a maximum of 90 days after the screening, we will perform the baseline visit and participants will receive the first dose of IMP under strict monitoring.

From this point forward, the first 18-months phase treatment regime begins, and it is divided into the titrations phase and the maintenance phase. Initially, each participant will receive five intra-participant IMP dose escalations at 60 mg TID (baseline – day 7), next 120 mg TID (days 8–14), 315 mg BID (days 15–28), 315 mg TID (days 22–28), and 420 mg TID, a total of 1,260 mg/d. To track the side effects tied to the study drug, all patients will receive a weekly phone call in the dose-escalation phase to monitor safety and tolerability. Changes in medication use (other than the study drug), any AEs or falls will also be assessed during these phone calls. In the case of side effects, the PI can decide to deviate from the drug admission protocol in order to adjust or delay dose escalation.

All participants will have eight scheduled on-site visits: an initial screening, a drug administration visit, 6 follow-up visits, and a total 16 phone calls spread out over 18 months. Figure 1 shows the flow chart of the ANeED study’s schedule.

**Figure 1 fig1:**
[figure not shown]
The flow chart of the ANeED study’s schedule.

### Safety monitoring

During the follow-up visits, the physical examination, vital signs, ECG, MDS-UPDRS, neurological examination and laboratory measures will be repeated. We will monitor and register all AEs since the last visit. The clinical investigator (CI) will be responsible for reviewing each AEs, estimating its severity and possibility of relationship to IMP and finally deciding whether this is an indication to cease medication. We will register and report all AEs, regardless of their relation to trial treatment.

In life-treating conditions, the PI in each centre will handle suspicions of possible severe interactions and requests from the other clinician responsible for the patient.

### Primary outcome

The primary outcome is the mean score on the MMSE-N3 at 18 months in the intervention group compared to the control group. Secondary outcomes are as follows:

1. To establish safety and tolerability of the ABX in high doses. The endpoints are the number of participants withdrawing the study medication in ABX and placebo groups, the number of participants requiring reduction of dosage due to possible AE in ABX and placebo groups and the number and characterisations of AEs in both study arms.2. To establish the effect of ABX in subgroups of participants diagnosed with DLB measured by MMSE-NR3 in ABX and placebo groups dependent on stratified risk for concomitant beta-amyloid pathology defined by *APOE* status and beta-amyloid (Aβ_1-42_) levels in CSF.3. To assess the effect of ABX on the results of neuropsychological tests (change from baseline to 18 months in mean scores for the clock drawing test, COWAT immediate and delayed recall, TMT A and B, VOSP silhouettes and FAS test).4. To study the effect of ABX on the global functional decline measured by changes in CDR-SB at the baseline and after 18 months.5. To investigate the effect of the ABX on neuropsychiatric symptoms and depression measured by the mean change in the total NPI score and GDS, respectively, from baseline to the study end at month 18.6. To examine the effect of ABX on sleep disturbances, especially REM sleep behaviour disorders (RBD), frequency of falls, cognitive and awareness fluctuations, parkinsonism and autonomic functions. Endpoints are change in the number of participants with RBD defined from the MSQ, the frequency of falls at the baseline and study end, the change in the MFS and the mean change in the UPDRS motor part score at the baseline to month 18 in ABX and placebo arms.

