### Design

This is a multicentre, phase IIa, double blinded, randomised and placebo-controlled clinical trial, using a parallel arm design for 18 months’ follow up. The allocation ratio is 1:1 (treatment:placebo). The participants will undergo detailed clinical assessments at the screening visit, baseline visit (day 1) and at weeks 4, 8, 24, 36, and 52 of the treatment phase. We will perform four phone controls in the escalation phase and at week 5, 12, 16, 20, 28, 32, 40, 44, and 48. Between screening visit and baseline (max. 90 days), we will perform mandatory lumbar punctures, MRI, DaTSCAN, ECG, rsEEG, blood analysis, clinical and cognitive assessments.

Each participant will receive five intra-participant dose escalations at 60 mg three times a day (TID) (days 1–7), 120 mg TID (days 8–14), 315 mg twice a day (BID) (days 15–28), 315 mg TID (days 22–28) and 420 mg TID (days 29–550) with ABX or placebo for the duration of 18 months. After this period, we will offer the treatment with ABX in an open-label extension phase for 12 months for all participants who will continue.

The study is carried out in seven Norwegian centres: Helse Fonna, Haugesund Hospital as the study-coordinating center and Haraldsplass Deaconess Hospital (Bergen), Stavanger University Hospital, Akershus University Hospital (Oslo), Oslo University Hospital, St. Olav Hospital (Trondheim) and the University Hospital of North Norway (Tromsø) are allocated study sites. The inclusion period began in May 2021.

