### Participants

Participants must fulfil the following inclusion criteria: a) diagnosis of possible or probable DLB or MCI-DLB according to the established McKeith criteria from 2017 and 2020, respectively (McKeith et al., 2017; IG et al., 2020), b) are in age range between 50 and 85 years, c) have MMSE score > 15 at screening, d) are on stable doses of antiparkinsonian or dementia or psychiatric medications at least 1 month prior to the study initiation, e) participant or participant’s caregiver are able to give informed consent to actual and further assessments and procedures and f) have a responsible caregiver >18 years old who has contact with the participant at least three times a week.

The main exclusion criteria are a) any clinically significant or unstable psychiatric, medical or surgical condition, b) major cardiovascular or cerebral event that occurred within 6 months prior to the first visit, c) advanced malign disease or other terminal illness, d) relevant medication, alcohol or drug abuse, e) known sensibility to or contraindication for ABX, f) female participants who are pregnant or currently breastfeeding, and g) not able to proceed with the study regime (i.e., like traveling to study site or dysphagia, or unable to perform supplementary examination because of contraindications, claustrophobia, etc.). For other detailed inclusion and exclusion, criteria see Table 2.

**Table 2 tab2:** Inclusion and exclusion criteria in the ANeED study.

Inclusion criteria	1. Age ≥ 50 and ≤ 85 years of age, both gender
	2. Confirmed diagnosis of DLB including mild cognitive impairment in DLB (DLB-MCI).
	3. MMSE score >=15 at screening
	4. Able and willing to provide informed consent prior to any study related assessments and procedures
	5. Capable of complying with all study procedures
	6. Willing to provide blood samples for genetic analyses of APOE and GBA
	7. Willing and able to self-administer or administer by a caregiver oral ambroxol medication, from day 1 to study end (at 60 mg TID (day 1-7), 120 mg TID (day 8- 14), 315 mg BID (day 15-21), 315 mg TID (day 22-28) and 420 mg TID (day 29-550)).
	8. Contact with caregiver at least 3 times a week, to ensure sufficient information from the caregiver regarding participant’s status and possible change in condition
	9. Able to travel to the participating study site

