### Sample size

The primary outcome in this study is the mean score between the two groups (placebo and ABX) at 18 months. Both groups included patients with prodromal DLB and DLB. Based on our published data from the Dementia Study of Western Norway, where we included persons living with mild DLB (MMSE 23 points average at baseline) with annual follow-up, we found that the annual decline during the first 2 years of follow-up is 2 points for DLB with a standard deviation of 5.7. Based on these data, we estimated a 3-point decline at 18 months. We applied a sample power analysis to calculate the number of participants needed to detect a 3-point difference in the MMSE-NR3 scores at 18 months for 80% power to find a difference between the active treatment group and the placebo group and accounted for 25% drop-out. Based on these data, we estimated the sufficient number of participants to be 180.

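### The falls endpoint compares two time points with no stated window, and so leaves most of the 550-day follow-up unused for a recurrent event

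*Protocol article*

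**What the plan says.** The Primary outcome section of the protocol article also lists the secondary outcomes. Number 6 covers sleep, falls, fluctuations, parkinsonism and autonomic function, and its falls endpoint is "the frequency of falls at the baseline and study end". No look-back period is given for either frequency. Outcome 5 in the same list places study end at month 18.

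On data collection, Interventions and assessment procedures states that "all patients will receive a weekly phone call in the dose-escalation phase to monitor safety and tolerability", and the next sentence adds that "any AEs or falls will also be assessed during these phone calls". The same section gives "a total 16 phone calls spread out over 18 months". Safety monitoring says of the follow-up visits: "We will monitor and register all AEs since the last visit". Falls are not named there.

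The article gives no fall rate, no power and no analysis model for falls. Statistical methods leaves full analysis detail to the SAP, which is not shown.

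**The concern.** The other measures in outcome 6 are a status or a scale score (REM sleep behaviour disorder, fluctuations, UPDRS motor part). A comparison of baseline with month 18 is natural for these. Falls are events that accumulate, so the information lies in the count over the whole period at risk. Restricting the endpoint to two time points leaves out the falls in between, at least some of which the trial asks about. It also makes the endpoint depend on a month-18 assessment, which not every participant will have. Without a look-back period neither frequency can be computed at all.

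Falls bear on parkinsonism and fluctuations, and also on tolerability. An imprecise comparison could miss a difference between arms in either direction.

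**Working it through.** The article has no falls calculation to reproduce, so the check compares an end window with the full follow-up.

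**Inputs from the article.** Treatment runs to day 550 (Design; Table 2), which is 550/365.25 = 1.506 years. Sample size: "we estimated the sufficient number of participants to be 180". With 1:1 allocation and 25% drop-out this gives 90 × 0.75 = 67.5, taken as 67 completers per arm.

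**Assumptions, not in the article.** End window w of 28, 90 or 182 days; fall rate λ of 0.5 to 4 per year; negative binomial dispersion k of 0 to 2; a constant fall rate and a constant rate ratio over follow-up.

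**Step 1: follow-up time unused, 1 − w/550.**
- 28 days: 1 − 0.051 = 94.9%
- 90 days: 1 − 0.164 = 83.6%
- 182 days: 1 − 0.331 = 66.9%

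With a constant rate these are also the expected shares of falls not used.

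**Step 2: precision.** With equal rates in both arms, SE(log RR) = √[(2/n)(1/(λt) + k)], where n = 67 and t is the length of the counting period in years.

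Example with λ = 2 and k = 1:
- Full period: λt = 3.01, SE = √[(2/67)(0.332 + 1)] = 0.199
- 28 days: λt = 0.153, SE = √[(2/67)(6.52 + 1)] = 0.474

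The first and last rows below give the extremes of the range. Ratios to the full-period SE are in brackets.

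| λ, k | Full period | 28 days | 90 days | 182 days |
|---|---|---|---|---|
| 0.5, 0 | 0.199 | 0.882 (4.43) | 0.492 (2.47) | 0.346 (1.74) |
| 2, 1 | 0.199 | 0.474 (2.38) | 0.301 (1.51) | 0.245 (1.23) |
| 4, 2 | 0.254 | 0.396 (1.56) | 0.300 (1.18) | 0.273 (1.07) |

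With k = 0 the ratio is √(550/w) whatever the fall rate.

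**Step 3: power by simulation.** Settings: 67 per arm, gamma-distributed individual rates with k = 1, true rate ratio 0.6, two-sided 5% test on mean counts, 2,000 runs per setting. The treated arm has its own lower mean. At λ = 2 the full-period count has power of 68% to 70% across runs. For 28, 90 and 182 days:
- End window alone: 14%, 34% and 49%
- Change from baseline to end window: 11%, 23% and 39%

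The gap narrows when falls are frequent and the window is long. At λ = 4 and 182 days, change from baseline has 66% against 74% for the full period.

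**Step 4: who contributes.** The planned drop-out is 0.25 × 180 = 45 participants. Those not assessed at month 18 have no study-end value. A person-time analysis would use their follow-up until last contact. Steps 2 and 3 do not credit that gain, because both use completers only.

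**Step 5: contacts available.** Design lists four escalation calls and nine more at weeks 5 to 48, so 13 of the stated 16 can be placed in time. Contacts at which falls could be asked about therefore exist well beyond escalation.

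**The case against.** The strongest reply is that the article leaves the window undefined and the SAP may define it. A six-month window would leave about two thirds of follow-up unused, not nearly all, and the SE could be only 7% larger. That stands as a limit on size. It does not remove the point, because the article itself fixes the two time points, and an SAP that follows it inherits them.

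Second, collection of falls throughout the 18 months is an inference. The sentence on falls refers back to the weekly escalation calls, and Safety monitoring registers AEs without naming falls. That also stands, and it is why the remedy needs the question asked at every contact.

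Third, a reader might infer that falls in participants who stop treatment are ignored by the trial. The article does not support this. Secondary outcome 1 counts AEs and withdrawals from study medication in both arms, so a fall recorded as an AE is counted there. What is lost is its use in the falls endpoint.

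Fourth, a disease-modifying effect might grow with time, and an end window would then look where the effect is largest. This is fair, since the working assumes a constant rate ratio. At λ = 2 and k = 1, however, the log rate ratio in the window would have to be about 2.4, 1.5 or 1.2 times the full-period average (28, 90 or 182 days) just to offset the larger SE.

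Last, this is one endpoint within one secondary outcome of a phase IIa trial. The primary MMSE comparison is unaffected.

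**Conclusion.** The point holds in limited form. The article states a two-point endpoint for a recurrent event, gives no look-back window, and does not use the falls asked about in between. An end window was less precise than a full-period rate under every setting of the formula. The SE ratio is 1.6 to 4.4 for 28 days, 1.2 to 2.5 for 90 days and 1.07 to 1.7 for 182 days. These ranges rest on assumed fall rates, dispersion and windows, and on a constant rate ratio.

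Two stronger readings should be avoided:
- That nearly all falls are discarded and precision is always far worse. This fits windows of about one to three months, but not six months with frequent, overdispersed falls.
- That the SEs convert directly into rate ratios detectable with 80% power through exp(−2.8 × SE). That shortcut puts the control mean in both arms. At 0.1 falls per month, k = 1 and a one-month window it gives a ratio of 0.20. With the treated-arm mean of 0.02, SE = √[(1/0.1 + 1/0.02 + 2)/67] = 0.96 and power is about 39%.

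The change is worth making, but it is not critical to the trial's main conclusion.

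**What to change.** Redefine the falls endpoint as the number of falls per person-time from first dose to month 18, or to last contact if earlier, in all randomised participants. Compare arms with a negative binomial model with log follow-up time as offset, adjusted for baseline fall frequency over a stated look-back period and for the stratification factors (APOE ε4 allele count and CSF beta-amyloid).

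Ask about falls since the last contact, in the same words, at every call and visit already scheduled.

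The cost is an amendment to the endpoint wording, the matching SAP text, and a uniform question on the contact forms. No new visits are needed. One limitation remains: the Discussion reports that 30 participants had already started medication, so for those already on treatment earlier falls may have to be taken from call and AE records. The SAP should say how this is done, without reference to treatment arm.

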### Ancillary studies

We will also perform a number of optional sub-studies:

1. Neurophysiological study using data from rsEEG registration at the baseline and at the end of the trial. This method is non-invasive and relatively cheap for detecting early changes in cerebral activity and may prove to be a viable marker for distinguishing DLB from AD. We aim to characterise rsEEG parameters in patients with DLB in comparison with AD and healthy age matched controls from the European DLB Consortium EEG database.2. Neuroimaging study based on MRI data. Cerebral MRI anatomical neuroimaging scans without contrast (3D T1, T2 (TSE + 3D FLAIR), DWI and SWI) will be carried out on either 1.5 or 3 T scanners depending on site.We will perform volumetric measurement and multi-modal and post-processing techniques to characterise patterns of cerebral pathology in the early stages of DLB. Additionally, it will be of interest to examine putative changes in these parameters before and after treatment with ABX.3. CSF fluid and blood biomarker studies. These will be planned to determine if treatment with ABX potentially has an effect on brain amyloidosis (Aβ_1-42_), tau-tangles (p-tau), and neurodegeneration (t-tau). To assess aS levels in CSF we chose CSF Real-Time Quaking-Induced conversion method. The genotyping will be performed for the presence of *GBA1* mutations and to determine APOE allele status. The GCase levels in serum will be taken, before treatment and at the end of treatment period.4. Remote disease and treatment monitoring study. As soon as possible, we will implement high-tech digital methods, such as smartphones, smart glasses, smart headbands and non-contact smart sleep monitor (Somnofy) to register the spectrum of vital signs, sleep parameters, motor activity and simplified EEG and eye tracking data. Additionally, we aim to implement real-time gait or walking activity monitoring to assess motor symptoms in DLB and changes under treatment.5. Caregivers’ stress study. Caregivers’ engagement is an integral part of a patient’s care but may often be connected with emotional and mental burnout. We wish to assess the caregivers’ stress levels and to find out what critical moments in patient care lead to distress. Such an analysis will be a starting point for developing of improvement procedures.

### Sample size

The primary outcome in this study is the mean score between the two groups (placebo and ABX) at 18 months. Both groups included patients with prodromal DLB and DLB. Based on our published data from the Dementia Study of Western Norway, where we included persons living with mild DLB (MMSE 23 points average at baseline) with annual follow-up, we found that the annual decline during the first 2 years of follow-up is 2 points for DLB with a standard deviation of 5.7. Based on these data, we estimated a 3-point decline at 18 months. We applied a sample power analysis to calculate the number of participants needed to detect a 3-point difference in the MMSE-NR3 scores at 18 months for 80% power to find a difference between the active treatment group and the placebo group and accounted for 25% drop-out. Based on these data, we estimated the sufficient number of participants to be 180.

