## Discussion

Here, we present here our protocol for the ANeED study testing ABX in prodromal and mild DLB. Prodromal stages of DLB are now defined for research purposes and these individuals, including those with mild dementia and those who need to be offered inclusion in clinical trials to establish treatment options with disease modifying drugs in DLB.

The rationale for the use of ABX in DLB is firmly established and is based on both preclinical and clinical data. Because GCase activity is associated with aS metabolism, enhancing CMA may potentially reduce pathological aS depositions. Preclinical trials of ABX in models of synucleinopathies are promising and showing the effects of reducing the concentration of toxic aS species. ABX penetrate into CSF (Mullin et al., 2020) and first trials have shown an enhancing effect of ABX on GCase activity in human cells.

Our study is the largest ongoing clinical trial with ABX and the first in patients with prodromal and mild DLB. To date, we have included 47 patients in the study and 30 who started medication in the first 12 months; we observed good tolerability with only a few side effects. There are also seven candidates waiting for a screening visit.

One previous study on ABX in PD was carried out in only 17 participants, and it was not randomised or placebo controlled (Mullin et al., 2020); another is now completed with 50 patients with PDD (Silveira et al., 2019). The goal in our study is to recruit 180 participants, a number sufficient to find a difference between the active treatment group and the placebo group at 18 months based on the MMSE. However, 180 participants might not be enough to apply for a marketing authorisation if the study turns out to show the effect of ABX on DLB.

Based on our previous research, we know that the combined significant AD pathology in DLB will worsen prognosis; therefore, we decided to stratify the participants in our study based on APOEε4 genotypes and CSF Aβ_1-42_ to secure equal groups for placebo and ABX. We will also extend the study duration to 18 months and thereafter to 12 months of open extension to maximise the chances of showing treatment effects.

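### The 3-point target and the SD of 5.7 come from a mild-DLB cohort, but the arms also enrol prodromal patients, and the protocol does not show that the cohort decline applies to the mixed placebo arm

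*Protocol article*

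**What the plan says.** The Sample size section describes the trial population as mixed: "Both groups included patients with prodromal DLB and DLB". The planning figures come from the sponsor's earlier cohort, "where we included persons living with mild DLB (MMSE 23 points average at baseline) with annual follow-up". From it the section reports that "the annual decline during the first 2 years of follow-up is 2 points for DLB with a standard deviation of 5.7", and then "we estimated a 3-point decline at 18 months". The same 3 points serve as the between-arm difference to be detected with 80% power. With 25% drop-out allowed for, the stated total is 180.

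The Participants section confirms the broader population. It admits a "diagnosis of possible or probable DLB or MCI-DLB according to the established McKeith criteria from 2017 and 2020, respectively". The only MMSE limit is a floor, "have MMSE score > 15 at screening" (Table 2 has 15 or above). No upper limit and no planned share of MCI-DLB is given.

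The Randomisation and blinding section stratifies by APOE ε4 count and CSF beta-amyloid, not by disease stage. The Statistical methods section plans an ANCOVA of 18-month MMSE on treatment and baseline MMSE, with a random intercept for stratum and block. The Discussion calls 180 "a number sufficient to find a difference between the active treatment group and the placebo group at 18 months based on the MMSE".

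**The concern.** The control decline and the SD describe one population, and the trial enrols a broader one. In many designs a modest mismatch of this kind is cushioned because the target is well below the control decline. Here there is no cushion. The target equals the entire decline that placebo patients are assumed to suffer, and a treatment that slows or halts decline can save at most what placebo patients lose. If the mixed placebo arm loses less than 3 points in 18 months, complete arrest of decline would still fall short of the planned difference. A null result could then partly reflect case mix and be read as lack of effect. If the mixed arm loses 3 points or more, this problem does not arise. The document gives the reader no means of telling which applies.

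**Working it through.** **Inputs from the protocol article.** Decline 2 points a year, SD 5.7, target difference 3 points, power 80%, drop-out 25%, N = 180 (Sample size); allocation 1:1 (Design).

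**Assumptions not in the document.** Two-sided alpha of 0.05 and a two-sample t-test. Where a placebo decline below 3 points is considered, treatment is taken to remove all of it, as the plan's own target implies.

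**1. The plan's own figures.** Decline at 18 months: 2 × 1.5 = 3 points. The t-test needs 57.6, so 58 per arm, for 3 points at SD 5.7 and 80% power. That is 116 in total, and 116 / 0.75 = 155 enrolled. The stated 180 is larger and is not reproduced from the stated inputs. That is a separate matter; the figures below give the plan full credit for 180.

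**2. Power at N = 180.** Completers per arm: 180 × 0.75 / 2 = 67.5. The difference detectable with 80% power is 2.77 points, a margin of 3 − 2.77 = 0.23 points, or about 8% of the assumed decline.

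**3. What a different case mix would do.** With a share p of MCI-DLB participants whose decline is a fraction r of 3 points, the pooled placebo decline is 3 × (1 − p(1 − r)). Both p and r are illustrative.

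| p | r | Pooled decline = largest difference from halting decline | Power, t-test, SD 5.7 |
|---|---|---|---|
| any | 1 | 3.00 | 86% |
| 0.3 | 0.75 | 2.78 | 80% |
| 0.3 | 0.5 | 2.55 | 73% |
| 0.4 | 0.5 | 2.40 | 68% |
| 0.5 | 0.5 | 2.25 | 62% |

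The rows use r of 1 or less because only a smaller decline threatens the target. If the mixed arm declined faster than the cohort, the pooled figure would exceed 3 and power would exceed 86%; at 3.3 points, for example, it is 92%.

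**4. Effect of the planned ANCOVA.** If 5.7 is the SD of 18-month scores, adjustment for baseline MMSE with correlation ρ reduces the residual SD to 5.7 × √(1 − ρ²). The document gives no ρ.

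| ρ (assumed) | Residual SD | Detectable at 80% power | Power at 2.40 | Power at 2.25 |
|---|---|---|---|---|
| 0 | 5.70 | 2.77 | 68% | 62% |
| 0.3 | 5.44 | 2.64 | 72% | 67% |
| 0.5 | 4.94 | 2.40 | 80% | 75% |
| 0.6 | 4.56 | 2.22 | 86% | 81% |

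If 5.7 is already the SD of change, which the wording also allows, the gain would be smaller. The text does not settle which it is.

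**The case against.** The strongest reply is that the power statement is conditional and is met. The section claims 80% power for a 3-point difference, and 180 with 25% drop-out gives 86% for that difference under the assumptions above. This stands. A reader might infer that the stated power is wrong, or wrong by a known amount; the document does not support that.

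A reader might also infer that prodromal patients decline more slowly, because the Background section says that symptoms are less pronounced at that stage. That sentence argues for biomarkers in diagnosis and concerns the level of symptoms at presentation. It does not concern MMSE points lost over 18 months. Nothing in the document gives a rate for MCI-DLB. Case mix could also differ in the other direction: with an MMSE floor of about 15, patients well below the cohort mean of 23 are eligible, and their rate of decline is not given either.

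The planned ANCOVA is a further fair point. At ρ = 0.5 it restores 80% power at 2.40 points if 5.7 is the SD of 18-month scores. It cannot be relied on without a stated correlation, and the sizing does not claim it.

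Finally, the point overlaps with the choice of full arrest of decline as the target, since all the scenario powers use that premise. This too stands: the mismatch of populations matters as much as it does because the target equals the decline.

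The mismatch itself remains. It is not a detail left to a fuller document: the article states its sizing basis and its population in the same paragraph, and they differ.

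**Conclusion.** The sizing rests on a decline and an SD from mild DLB, while the trial enrols mild and prodromal DLB, and nothing in the document links the two. Since the target equals the whole assumed decline, power for an attainable effect depends on that missing link. Neither direction nor size can be established from the document. As a guide, with an unadjusted comparison at SD 5.7 and two-sided 0.05, the planned 80% holds down to a pooled placebo decline of 2.77 points and falls to 68% at 2.40 and 62% at 2.25. Baseline adjustment may offset part or all of this. The Discussion's unqualified statement that 180 is sufficient goes further than the sizing basis allows. The point is worth correcting, but it does not show that the trial is underpowered.

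**What to change.** Keep N at 180.

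- **Sample size:** state the expected MCI-DLB share, or the share to date taken blinded to arm, together with the 18-month decline and SD assumed for the mixed placebo arm and their source. Do not presume that the MCI-DLB decline is lower. Say whether 5.7 is the SD of the score or of change.
- **Power:** present it as conditional on that decline, with a short sensitivity table under the planned ANCOVA that covers a range of pooled declines and baseline correlations.
- **Discussion:** qualify the sufficiency statement to match.
- **Statistical methods:** add diagnosis at entry (MCI-DLB versus DLB) as a prespecified fixed covariate beside baseline MMSE. It is established at eligibility and is not a stratification factor. The analysis plan is to be completed before database lock, so this can still be prespecified.

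The cost is a few sentences, a possibly less favourable stated power, and one extra covariate that is already recorded. No patients or procedures are added.
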